**Annex 3: Clinical Total Impression Scale (CGI)****I. Severity of disease (CGI-S)**

Combine your overall clinical experience with this particular population, how serious is the patient's condition at this time?

**0=Unrated 4=Moderately sick**

1 = normal, completely disease free 5 = obviously sick

2 = marginal psychosis 6 = serious illness

3=Slightly sick 7=The disease is extremely serious

**II. Overall Progress (CGI-I)**

At your discretion, this improvement is entirely due to the treatment of the drug. How does the patient's condition change compared to when the patient was enrolled in the interview?

0 = not rated 4 = no change

1=Advance is very obvious 5=Slightly worse

2=Advance is obvious 6=Significantly worsened

3=Slight progress 7=Deterioration is very obvious

**Annex 4: Hamilton Anxiety Scale (HAMA)**

*All items used a 5-level scale of 0 to 4 points. The standards at each level are: (0) non-existent; (1) mild; (2) moderate; (3) severe; (4) very serious.*

| project      |                                                                                                               | score |
|--------------|---------------------------------------------------------------------------------------------------------------|-------|
| Anxious mood | Worried, the hunch has the worst thing to happen, feels scared, easy to provoke                               | _     |
| Nervous      | Feelings of tension, fatigue, shocking reaction, tearing after shaking, shaking, feeling uneasy, not relaxing | _     |

|                                    |                                                                                                                                                            |   |
|------------------------------------|------------------------------------------------------------------------------------------------------------------------------------------------------------|---|
| Fear                               | Fear of darkness, strangers, alone, animals, cars, or people                                                                                               | _ |
| 4. Insomnia                        | Difficult to fall asleep, easy to wake up, sleep poorly and feel tired after waking up, dreaming, nightmares, night terrors                                | _ |
| 5. Memory or attention disorder    | Intention can not concentrate, memory is poor                                                                                                              | _ |
| 6. Depressed mood                  | Losing interest, lack of pleasure in past hobbies, depression, early waking, squatting                                                                     | _ |
| 7. Muscle symptoms                 | Muscle soreness, muscle twitching, inflexible activity, myoclonic convulsions, molars, trembling, increased muscle tone                                    | _ |
| 8. Feeling symptoms                | Tinnitus, blurred vision, cold and fever, weakness, tingling                                                                                               | _ |
| 9. Cardiovascular symptoms         | Tachycardia, heart palpitations, chest pain, vascular motility, fainting, heartbeat leakage                                                                | _ |
| 10. Respiratory symptoms           | Chest tightness or tightness, suffocation, sigh, difficulty breathing                                                                                      | _ |
| 11. Gastrointestinal symptoms      | Dysphagia, abdominal pain, burning, bloating, nausea, vomiting, bowel, diarrhea, weight loss, constipation                                                 | _ |
| 12. Genitour urinary symptoms      | Frequent urination, urgency, amenorrhea, menstrual flow, cold, premature ejaculation, loss of libido, impotence                                            | _ |
| 13. Autonomic symptoms             | Dry mouth, flushing, paleness, sweating, dizziness, tension headache, hair erection                                                                        | _ |
| 14. Performance during the meeting | Sitting restless, irritated or pacing, shaking hands, frowning, stiff expression, sighing or shortness of breath, pale, swallowing from time to time, etc. | _ |
| Total score  _              |                                                                                                                                                            |   |

**Annex 5: SHEEHAN Disability Scale (SDS)**

A brief assessment of disability and defects by patient self-assessment

Please mark only one circle for each rating scale.

**Work \* or school**

Symptoms affect your work or study:

Not at all      Mild      Moderate      Obvious      Extrem

① ← ----- ①-----②-----③-----④-----⑤-----⑥-----⑦-----⑧-----⑨----- → ⑩

☐ Over the past 1 weeks, I have not worked or studied for reasons related to illness.

\* Work includes paid work, unpaid work or training.

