#### **The secondary efficacy endpoint**

- Changes from baseline in the 17 items Hamilton Depression Scales (HAM-D17) total scores at the end of treatment.
- Clinical Global Impression – global improvement (CGI-I) scores at the end of treatment.
- Changes from baseline in the Clinical Global Impression –severity illness (CGI-S) scores at the end of treatment.
- Changes from baseline in the the Hamilton Anxiety Scale (HAMA) total scores and factor scores at the end of treatment.
- Changes from baseline in the HAM-D17 factor scores at the end of treatment.
- Response rate in MADRS at the end of treatment (Response means that the reduction in MADRS score is 50% or more relative to the baseline value).
- Response rate in HAM-D17 at the end of treatment (Response means the reduction in the HAM-D17 scores is 50% or more relative to the baseline values).
- Remission rate in MADRS at the end of treatment (Remission refers to MADRS  $\leq 12$ ).
- Remission rate in HAM-D17 at the end of treatment (Remission refers to HAM-D17  $\leq 7$ ).
- Changes from baseline in the SHEEHAN Disability Scale (SDS) total scores at the end of treatment.

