#### **11.2.2.7 Processing of missing data**

The Mixed-Effect Model Repeated Measure (MMRM) will be used to analysis the total score of MADRS, HAM-D17, HAMA and SDS for missing data. The LOCF methods was used to impute the missing data and ANCOVA model was used for sensitivity analysis.

For MADRS response rate, HAM-D17 response rate, MADRS remission rate and HAM-D17 remission rate, the predicted value from MMRM model will be used to imput the missing data, and this analysis will be considered as primary analysis results.

The analysis results of the MADRS response rate, HAM-D17 response rate, MADRS remission rate, HAM-D17 remission rate based on the LOCF imputation will be considered as sensitivity analysis.

The rest of endpoints efficacy evaluation, including HAM-D17 single item scores, HAMA single item scores, CGS-S score, CGS-I score, the LOCF method was used to impute the missing data.

This study will not perform any missing data imputation for safety endpoint.

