#### Number of days absent from absence

In the past week, how many days have you been unable to complete your normal day-to-day duties due to your symptoms?

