### **Appendix**

#### **SDS assessment instructions**

This scale is a self-rating scale, which is mainly used to assess the functional status and efficacy of patients with mood disorders or anxiety disorders. A survey of patients attending primary care centres showed that the internal consistency of the scale was good with an alpha coefficient of 0.83.

Evaluate the situation of the last 7 days before the interview.

The assessment includes work, social life, and family life; related items include days of absence and days of inefficiency.

Each entry is divided into 11 levels of 0 to 10 points, with a total score of 0 to 30 points.

**Annex 6: Colombia - Suicide Severity Rating Scale (C-SSRS)****7-1 Colombia - Suicide Severity Rating Scale - Screening/Baseline**

| Suicidal ideation                                                                                                                                                                                                                                                                                                                                                                                                                                                                                                                                                                                                                                                |                                                                             |                                                                         |
|-------------------------------------------------------------------------------------------------------------------------------------------------------------------------------------------------------------------------------------------------------------------------------------------------------------------------------------------------------------------------------------------------------------------------------------------------------------------------------------------------------------------------------------------------------------------------------------------------------------------------------------------------------------------------|-----------------------------------------------------------------------------|-------------------------------------------------------------------------|

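### The only alternative box on the printed SDS work item is for patients off work through illness, probably a lost negation; if used as printed, it can cost those patients their work rating and distort the 0-30 total

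*Protocol*

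**What the plan says.** Section 8.1 of the protocol lists as a secondary endpoint "Changes from baseline in the SHEEHAN Disability Scale (SDS) total scores at the end of treatment". Annex 5 prints the form, which patients complete themselves. Its general instruction is "Please mark only one circle for each rating scale". Under the work or school scale there is one tick box, worded "Over the past 1 weeks, I have not worked or studied for reasons related to illness", and a footnote: "Work includes paid work, unpaid work or training". The social and family scales have no box.

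The SDS assessment instructions in the same annex describe the content as follows: "The assessment includes work, social life, and family life; related items include days of absence and days of inefficiency". They give the scoring as "Each entry is divided into 11 levels of 0 to 10 points, with a total score of 0 to 30 points". They do not say whether a ticked box replaces the circle or what value it takes.

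Section 11.2.2.4 analyses the SDS total by the same method as the primary endpoint. It also summarises and compares the change in each SDS item. Section 11.2.2.7 says that the mixed model for repeated measures "will be used to analysis the total score of MADRS, HAM-D 17 , HAMA and SDS for missing data". It gives no rule for an unrated SDS item.

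**The concern.** A box beside a rating scale invites the patient to tick it instead of rating. As printed, the invitation goes to the wrong people. A patient who did not work or study because of depression has the outcome that the item exists to record. A patient with no work or study for another reason has nothing for the item to measure, has no box, and so gives an uninformative rating.

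The protocol's other scales agree that absence through illness is severe. Item 7 of the HAM-D17 in Annex 2 gives its top score of 4 when work has stopped because of the current illness. The SDS form offers the same patients an unscored alternative.

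At stake is the validity of the SDS total. It is the only functional scale among the secondary endpoints, and a rating that was never given cannot be recovered at analysis.

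**Working it through.** **Range of the total.** Annex 5 gives three domains (work, social life, family life), each scored 0-10.

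- All three rated: 3 x 10 = 30, which reproduces the stated 0-30.
- Work unrated and the other two summed: 2 x 10 = 20.

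The stated range therefore presupposes a work rating. The separate question on days lost ("how many days have you been unable to complete your normal day-to-day duties due to your symptoms") does record illness absence, but the annex treats it as a related item. The 30 points are already used up by the three domains.

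**What a missing work rating does to one patient.** The protocol gives no SDS data, so the ratings here are assumed. At baseline the patient is off work through illness, ticks the box and gives no work rating; social is 7 and family 7. At week 8 the patient is back at work: work 4, social 6, family 6, total 16.

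| Treatment of the ticked box | Baseline | Week 8 | Change |
|---|---|---|---|
| Sum of rated items | 7 + 7 = 14 | 16 | +2 |
| Total set to missing | none | 16 | none |
| Pro-rated by 3/2 | 14 x 1.5 = 21 | 16 | -5 |
| Absence counted as 10 | 10 + 14 = 24 | 16 | -8 |

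The patient improved in both rated domains and returned to work. Summing the rated items reports a worsening, 10 points away from the result with absence scored as full impairment.

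**When the sign turns.** If rated items are summed, the recorded change is the week 8 work score minus the combined fall in the social and family scores. It reads as worsening only if the work score is larger than that fall. Above, 4 - (1 + 1) = +2.

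With larger gains elsewhere it does not turn. Take a patient whose true ratings are 9, 7, 7 at baseline and 4, 4, 4 at week 8. The true change is 12 - 23 = -11. With the baseline work rating left blank, the recorded change is 12 - 14 = -2: improvement is masked, not reversed.

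**The opposite direction.** A patient rated 6, 7, 7 (total 20) stops work through illness, ticks the box, and rates social 8 and family 8.

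- Sum of rated items: 16 - 20 = -4, an apparent improvement.
- Pro-rated: 24 - 20 = +4.
- Absence counted as 10: 26 - 20 = +6.

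**Is the wording likely to be a slip?** Annex 6 has a similar fault: the first C-SSRS question pairs wanting to die with hoping to wake up after falling asleep, where the sense requires not waking. A lost negation in the SDS box fits that pattern.

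**The case against.** The strongest reply is that the harm depends on steps the protocol does not state. The annex asks for one circle on every scale and exempts nobody, so a patient off sick could mark a circle and tick the box as an extra flag, and nothing would be lost. The 0-30 range points the same way. Sign reversal needs the further rule that rated items are summed; it does not occur when the total is set to missing or absence is scored 10, nor with pro-rating in the example. Missing-item rules are commonly left to the SAP, which is not at hand. The fault may also exist only in the English rendering.

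Most of this stands, and it limits the point to a conditional one. It does not remove it. The complaint is not that a scoring rule is absent but that the printed box singles out the wrong patients, and no SAP rule can restore a rating that a patient was invited to skip. An SAP that treated a ticked box as not applicable would drop the most work-disabled patients.

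A reader might go further and infer a bias against the drug. Suppose 10-30% tick the box at baseline, 60% on drug and 45% on placebo return to work, and each omitted work score is 9. The understatement is then 0.1 to 0.3 x 0.60 x 9 = 0.54 to 1.62 points on drug and 0.1 to 0.3 x 0.45 x 9 = 0.41 to 1.22 on placebo, a difference of about 0.14 to 0.41. Every one of these inputs is assumed. The protocol reports no employment, sick-leave or return-to-work figures, so it supports neither the size nor the direction of a difference between arms.

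It would also be too strong to say that everyone without a job is forced to invent a rating. The footnote counts unpaid work and training as work, which narrows that group without emptying it.

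**Conclusion.** The point holds in conditional form. The box as printed in Annex 5 is wrong and probably reflects a lost negation. Two conditions are needed for harm: the wording is on the form patients actually use, and the box is ticked in place of a circle. Patients off work through illness then lose their work rating. Their total is either missing or, under the additional assumption that rated items are summed, limited to 20, and a return to work can mask improvement or read as worsening. For single patients with assumed ratings, summing departs from the alternative scoring by 9 or 10 points. Separately, patients with no work or study for unrelated reasons contribute uninformative work ratings.

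The protocol does not support the claim that SDS data in this trial are distorted, or that one arm is favoured: the frequency cannot be estimated. The reach is limited to one secondary endpoint. The multiplicity procedure in 11.2.2.6 covers MADRS only, and the primary analysis and sample size are unaffected.

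**What to change.** 1. Compare the Annex 5 box with the form given to patients at the sites. If the site form already refers to reasons not related to illness, only the protocol text needs correcting.
2. Correct the box so that it covers patients who did not work or study for reasons NOT related to illness.
3. State on the form that everyone else, including patients off work because of illness, must mark a 0-10 work rating.
4. State in the Annex 5 scoring instructions or in 11.2.2.4 that the SDS total is formed only when all three items are rated.

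The separate analysis of SDS items is already in 11.2.2.4 and need not be added.

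The cost is one form line and two short instructions. The downside is that patients with no work or study for other reasons will have no SDS total, which reduces the number analysed for this secondary endpoint; their social and family ratings remain available for the item analysis.

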**Social life**

Symptoms affect your social life or leisure activities

Not at all      Mild      Moderate      Obvious      Exterm

① ← ----- ①-----②-----③-----④-----⑤-----⑥-----⑦-----⑧-----⑨----- → ⑩

**Family life or family responsibilities**

Symptoms affect your family life or your family's contribution

Not at all      Mild      Moderate      Obvious      Exterm

① ← ----- ①-----②-----③-----④-----⑤-----⑥-----⑦-----⑧-----⑨----- → ⑩

#### Number of days absent from absence

In the past week, how many days have you been unable to complete your normal day-to-day duties due to your symptoms?

#### Inefficient days

In the past week, even if you go to school or go to work every day, how many days are there because your symptoms make you feel obstructed and the efficiency is reduced?

### **Appendix**

#### **SDS assessment instructions**

This scale is a self-rating scale, which is mainly used to assess the functional status and efficacy of patients with mood disorders or anxiety disorders. A survey of patients attending primary care centres showed that the internal consistency of the scale was good with an alpha coefficient of 0.83.

Evaluate the situation of the last 7 days before the interview.

The assessment includes work, social life, and family life; related items include days of absence and days of inefficiency.

Each entry is divided into 11 levels of 0 to 10 points, with a total score of 0 to 30 points.

**Annex 6: Colombia - Suicide Severity Rating Scale (C-SSRS)****7-1 Colombia - Suicide Severity Rating Scale - Screening/Baseline**

| Suicidal ideation                                                                                                                                                                                                                                                                                                                                                                                                                                                                                                                                                                                                                                                |                                                                             |                                                                         |
|-------------------------------------------------------------------------------------------------------------------------------------------------------------------------------------------------------------------------------------------------------------------------------------------------------------------------------------------------------------------------------------------------------------------------------------------------------------------------------------------------------------------------------------------------------------------------------------------------------------------------------------------------------------------------|-----------------------------------------------------------------------------|-------------------------------------------------------------------------|
| 
Ask questions 1 and 2. If the answer to both questions is no, please go to the "Suicide Behavior" section. If the answer to question 2 is "yes", please ask questions 3, 4, 5. If the answer to question 1 and/or the answer to question 2 is yes, complete the "Ideas Strength" section below.
                                                                                                                                                                                                                                                                                                                                                                  | In a lifetime:
the time
when you
most want to
commit
suicide | The past 6
months                                                    |
| 
1 hope to die
 
The subject acknowledged the idea of hoping to die or not to live, or the idea of waking up after falling asleep.
 
Have you ever wanted to die or hope to wake up after you fall asleep?
 
If yes, please describe:
                                                                                                                                                                                                                                                                                                                                                                                                | 
whether
 
 
     | 
whether
 
 
 |
| 
2 Unspecific active suicide ideas
 
During the assessment period, the idea of ending my life and committing suicide was general and not specific (such as "I thought about suicide"), but did not think about the way suicide, related methods, intentions or plans.
 
Have you ever thought of suicide?
 
If yes, please describe:
                                                                                                                                                                                                                                                                                                 | 
whether
 
 
     | 
whether
 
 
 |
| 
3 Active suicidal ideation with method (unplanned) but no intention of action
 
During the assessment period, the subject acknowledged the idea of suicide and thought about at least one suicide method, which is different from the specific plan that has time, place or specific method (such as thinking about suicide but not specific) s plan This includes someone who would say, "I thought about taking too much medication, but I never had a specific plan for when, where and actually to actually do it... and I will never do it."
 
Have you thought about how you would commit suicide?
 
If yes, please describe:
 | 
whether
 
 
     | 
whether
 
 
 |
| 
4 Active suicidal ideation with intention of action but no specific plan
                                                                                                                                                                                                                                                                                                                                                                                                                                                                                                                                                                                  | 
whether
                                                              | 
whether
                                                          |

|                                                                                                                                                                                                                                                                                                                                                                                                                 |                                                                  |                                                                  |
|-----------------------------------------------------------------------------------------------------------------------------------------------------------------------------------------------------------------------------------------------------------------------------------------------------------------------------------------------------------------------------------------------------------------|------------------------------------------------------------------|------------------------------------------------------------------|
| 
There is an idea of active suicide, and the subject says that there is an intention to implement these ideas, rather than "I have these ideas but I will definitely not implement them."
 
Have you had these ideas and have had the intent to implement them?
 
If yes, please describe:
                                                                                               |                  |                  |
| 
5 Active suicidal ideation with specific plans and intentions
 
The details of the plan for suicidal thoughts have been fully or partially developed and the subject has an intent to execute the plan.
 
Have you started to develop or have a detailed suicide plan?
 
Do you want to implement this plan?
 
If yes, please describe:
                         | 
whether
   | 
whether
   |
| Intensity of mind                                                                                                                                                                                                                                                                                                                                                                                        |                                                                  |                                                                  |
| 
The following characteristics regarding the most intense intentions should be assessed (eg, from 1 to 5 above, 1 is the lightest and 5 is the heaviest). Ask him (her) the time he most wants to commit suicide.
 
In life: the strongest idea: _____
 
Type number (1~5) meaning description
 
The past 6 months: the strongest idea: _____
 
Type number (1~5) meaning description
 | Strongest                                                        | Strongest                                                        |
| 
frequency
 
How many times have you generated these ideas?
 
(1) less than 1 time in 1 week
 
(2) Once a week
 
(3) 2 to 5 times a week
 
(4) 1 time per day or almost once a day
 
(5) Multiple times a day
                                                                                                                                                 | _____                                                            | _____                                                            |
| 
duration
 
How long will these thoughts last when you have suicidal thoughts?
 
(1) Short time - just a few seconds or minutes
 
(2) less than 1h/period of time
 
(3) 1~4h/long time
 
(4) 4~8h/almost 1d
                                                                                                                                                        | _____                                                            | _____                                                            |

|                                                                                                                                                                                                                                                                                                                                                                                                                                                                                                                                                                                                                                                                                                                                                                                                                                             |         |                   |
|---------------------------------------------------------------------------------------------------------------------------------------------------------------------------------------------------------------------------------------------------------------------------------------------------------------------------------------------------------------------------------------------------------------------------------------------------------------------------------------------------------------------------------------------------------------------------------------------------------------------------------------------------------------------------------------------------------------------------------------------------------------------------------------------------------------------------------------------|---------|-------------------|
| (5) more than 8h/lasting or continuous time                                                                                                                                                                                                                                                                                                                                                                                                                                                                                                                                                                                                                                                                                                                                                                                                 |         |                   |
| Controllability
If you want, can you stop suicide or hope to die?
(1) can easily control these ideas
(2) can control these ideas, almost no difficulty
(3) can control these ideas, but some difficulties
(4) can control these ideas, but it is very difficult
(5) can't control these ideas
(0) don't try to control these ideas                                                                                                                                                                                                                                                                                                                                                                                                                                                                       | _____   | _____             |
| Stopping factor
Is there any factor - someone or something (such as family, religion, pain of death, etc.) - has stopped your thoughts of wishing to die or committing suicide?
(1) The suppression factor has indeed stopped your suicide attempt
(2) The stopping factor may have stopped you
(3) Is it uncertain whether the stopping factor has stopped you?
(4) The stopping factor probably has not stopped you
(5) The suppression factor has never stopped you.
(0) Not applicable                                                                                                                                                                                                                                                                                                               | _____   | _____             |
| Causes of suicidal ideation
What are the reasons for your hopes of dying or committing suicide? Is it to end the pain or to end your feelings at the time (in other words, this pain or your feelings at the time prevents you from continuing to endure), or to arouse his attention, reaction or revenge? Or both?
(1) solely to attract the attention, reaction or revenge of others
(2) mainly to attract the attention, reaction or revenge of others
(3) It is to attract the attention, reaction or revenge of others, and to end or stop the pain.
(4) Mainly to end or stop the pain (you can't continue to endure this pain or the feeling at the time)
(5) It is all about ending or stopping the pain (you can't continue to endure this pain or the feeling at the time)
(0) Not applicable | _____   | _____             |
| Suicidal behavior
(As long as these suicidal behaviors are independent events, check all the content that matches: all types must be asked)                                                                                                                                                                                                                                                                                                                                                                                                                                                                                                                                                                                                                                                                                       | In life | The past 6 months |

|                                                                                                                                                                                                                                                                                                                                                                                                                                                                                                                                                                                                                                                                                                                                                                                                                                                                                                                                                                                                                                                                                                                                                                                                                                                                                                                                                                                                                                                                                                                                                                                                                                                                                                                                                                                                                                                                                                                                                                                               |                                                                                                          |                                                                                                          |
|-----------------------------------------------------------------------------------------------------------------------------------------------------------------------------------------------------------------------------------------------------------------------------------------------------------------------------------------------------------------------------------------------------------------------------------------------------------------------------------------------------------------------------------------------------------------------------------------------------------------------------------------------------------------------------------------------------------------------------------------------------------------------------------------------------------------------------------------------------------------------------------------------------------------------------------------------------------------------------------------------------------------------------------------------------------------------------------------------------------------------------------------------------------------------------------------------------------------------------------------------------------------------------------------------------------------------------------------------------------------------------------------------------------------------------------------------------------------------------------------------------------------------------------------------------------------------------------------------------------------------------------------------------------------------------------------------------------------------------------------------------------------------------------------------------------------------------------------------------------------------------------------------------------------------------------------------------------------------------------------------|----------------------------------------------------------------------------------------------------------|----------------------------------------------------------------------------------------------------------|
